### Aims and research questions

The main purpose of this study is to investigate how 80 min of prolonged sitting with and without frequent, short physical activity breaks of different intensities affects fNIRS-measured cerebral blood flow (measured as changes in oxygenated hemoglobin [oxy-Hb]) in the prefrontal cortex, in an ecologically valid mimicked classroom setting, during working memory tests of differential mental workloads in 13–14-year-olds.

Our primary research question is:

How does oxy-Hb in the prefrontal cortex during a working memory test change from before to after 80 min of prolonged sitting and after 80 min of sitting with physical activity breaks; and do these changes differ between these 80-min conditions?

Our secondary questions are:
Do physical activity breaks during prolonged sitting affect cognitive performance on the 1-, 2-, and 3-back tests; and self-reported psychological factors (stress, mood, alertness, and sleepiness)? Are these changes significantly different between conditions?Are the changes in cognitive performance correlated with changes in oxy-Hb?Does baseline arterial stiffness (measured as augmentation index and pulse wave velocity) moderate the change in cerebral blood flow and cognitive performance?Does the change in arterial stiffness mediate the changes in cerebral blood flow and cognitive performance?

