### Hypotheses

We hypothesize that:
Task-related increases in oxy-Hb will occur after the conditions involving physical activity breaks and will either stay the same or decrease after the prolonged sitting, and these changes will be significantly greater for the higher intensity break.Cognitive performance, specifically reaction time and accuracy on the n-back tests, will improve after the physically active conditions, but decrease or remain the same after the prolonged sitting condition. The changes will significantly differ between sitting with or without breaks of different intensities, such that more favorable changes will occur when the breaks are of higher intensity.There will be a correlation between changes in oxy-Hb and cognitive performance.Psychological factors, including cortisol-measured stress, and self-reported mood, alertness, and sleepiness, will improve after the physical activity break conditions, which will be significantly different from the prolonged sitting condition, where there will be no change.Arterial stiffness will be reduced after the physically active break conditions, and these changes will be different from the prolonged sitting condition, where no changes will occur or an increase will be observed.Changes in oxy-Hb will be mediated by changes in arterial stiffness.Baseline arterial stiffness will moderate the change in oxy-Hb and cognitive performance, such that there will be a more pronounced change in those with lower arterial stiffness.

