#### Cognitive performance

Cognitive performance in working memory will be assessed using a computerized *n*-back test [66], consisting of the 1-, 2-, and 3-back tests administered simultaneously with fNIRS measures. Participants will be required to indicate (via a key press within 2 s from stimulus onset) whether the digit presented on the screen was the same digit as the digit presented 1 stimulus previously (1-back), 2 stimuli previously (2-back), or 3 stimuli previously (3-back). Each digit will be presented for 1.5 s at an interstimuli interval of 500 ms. The n-back tests were created using E-Prime 2.0 (Psychology Software Tools). In order to reduce practice effects, participants will perform a shorter version (2 blocks) of the cognitive tests at the familiarization session and prior to data collection on each experimental day. The outcome variables for cognitive performance will include average reaction time (ms) and accuracy (average number of correct responses) for each test across 3 blocks of 20 digit sequences (see Fig. 2). There will be a 20-s rest between each set of 3 blocks, involving staring at a dot on the screen while internally counting up from 0 to allow for a short period of cognitive rest after instructions are presented on the screen. Practice tests with feedback will be provided before each testing followed by the actual testing without feedback. A task-based baseline was chosen (1-back), as rest is dynamic across age, and not considered an equalizer in younger age [67].

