### Statistical methods

Mixed effects models with subject as a random effect to assess within condition differences will be performed, and to examine time-by-condition interaction effects. Changes in arterial stiffness and PWV will be assessed in relation to cerebral blood flow changes in the mixed models.

Exploratory analyses will be performed excluding the short-separation regressors and ROI averages to compare to the main analyses.

Secondary outcomes (i.e., cognitive function, psychological factors, stress), will be assessed using mixed models, with the subject as a random effect, looking at both the within condition changes and the time-by-condition interaction effects. Correlational analyses will be performed to investigate the association between changes in cognitive function and cerebral blood flow if significant changes are seen. Maximum likelihood estimation will be used in the mixed models to handle missing data at random. Subsequent sensitivity analyses will be performed if necessary.

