There are many strengths of this trial, such as the use of state-of-the-art technology in measuring cerebral blood flow—fNIRS with short-separation channels. This can give more accurate results that have been lacking in previous studies [31–34, 41, 80]. The mimicking of the school environment (duration of 2 school lessons), and use of devices to measure physical activity and sedentary behavior provide more robust and ecologically valid estimates of pre-day physical activity and sleep behaviors. Additionally, the exercise paradigms are readily available to be implemented in school settings. Although the inclusion of a control group might be considered in a more potent study design, the randomized crossover design is a more attractive alternative as it allows the participants to be their own controls, thus reducing variability between individuals. Mind wandering may affect the participants as well as potential anticipatory affects due to awareness of the condition and subsequent conditions. However, the use of counting during the rest periods and randomization of the order of the conditions will help in minimizing these contaminations. Repositioning of the cap during test days may also reduce accuracy in measurement from pre-test to post-test, however, the use of a marker on the forehead will help to reduce misalignment. In addition, only the prefrontal cortex will be measured in this study, thus cortical activity in other regions cannot be measured. The experiments are to mimic a school day; therefore, generalizability to other settings or days of the week (i.e., weekend) needs to be carefully considered. Finally, this is the first study of this kind therefore subsequent studies will be required to confirm the results.

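### Within-condition pre-to-post tests stand level with the time-by-condition test, so a same-session trend could be read as an effect of the activity breaks

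*Protocol article*

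**What the plan says.** Under Statistical methods, the oxy-Hb analysis has two parts in one sentence: "Mixed effects models with subject as a random effect to assess within condition differences will be performed", followed by "and to examine time-by-condition interaction effects". For the secondary outcomes, which include n-back performance, the models are described as "looking at both the within condition changes and the time-by-condition interaction effects". No sentence says which of the two decides whether the breaks had an effect.

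The primary question, under Aims and research questions, opens with change over time: "How does oxy-Hb in the prefrontal cortex during a working memory test change from before to after 80 min of prolonged sitting". It puts the same question for sitting with breaks, and ends by asking whether the changes differ between conditions.

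Under Hypotheses, the first begins "Task-related increases in oxy-Hb will occur after the conditions involving physical activity breaks". It predicts no change or a fall after prolonged sitting, and its one explicit comparison is a larger change for the more intense break. The second says that reaction time and accuracy "will improve after the physically active conditions", and then does predict that changes differ between sitting with and without breaks.

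On repetition of the test, the Cognitive performance section says: "In order to reduce practice effects, participants will perform a shorter version (2 blocks) of the cognitive tests". This is done at familiarization and before data collection on each test day. The section also provides practice with feedback before each testing.

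**The concern.** A pre-to-post change within one condition has no comparator. On every visit the post-test is a repeat of the full n-back battery, taken after 80 minutes of mostly sitting. Whatever repetition or time on task does to the scores enters the SRA and STEP changes in full. Only the difference from SOCIAL removes it, because SOCIAL has the same tests and the same session length and comes in randomized order.

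Hypothesis 1 is the sharper case. Against sitting it states only a rise in one set of conditions and no rise in the other. That invites setting a significant result beside a non-significant one, which is not a test of the difference between them.

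At stake is a report that breaks raise task-related oxy-Hb or improve working memory when the controlled contrast shows nothing. There is also a knock-on: the correlation of cognitive with blood-flow changes is run only if significant changes appear, and the text does not say whether within or between conditions.

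**Working it through.** **The plan's own figure.** The Sample size section gives effect sizes of 0.9 to 2.4, two-sided alpha 0.05 and 0.8 (labelled beta, read here as power), leading to 6 to 13 participants, with 16 to be recruited. A paired t-test with noncentrality d√n gives n = 12 at d = 0.9 (power 0.81) and n = 4 at d = 2.4 (power 0.88). Both are within two participants of the stated range. These inputs size a single paired contrast; the section does not say whether that contrast is within or between conditions.

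**Structure.** Write the mean change in condition k as τ + β_k, where τ is a same-session trend common to all conditions and β_k is the condition's own effect.
- Within-condition test of STEP: estimates τ + β_STEP.
- STEP minus SOCIAL: estimates β_STEP − β_SOCIAL, and τ cancels.
- Oxy-Hb is analysed as 2-back and 3-back against 1-back (Cerebral blood flow section). A trend equal at all loads cancels there too; only a load-specific trend survives.
- Reaction time and accuracy are taken for each load with no such subtraction, so τ stays.

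**Inputs for the error rates.** From the document: n = 16, three conditions, two-sided alpha 0.05. Assumed: no break effect, τ between 0 and 0.9 SD of the change score in the hypothesised direction, and a correlation of change scores between conditions of 0 or 0.5. The document gives neither the size nor the direction of τ.

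**One condition, analytic.** The noncentrality is τ√16 = 4τ on 15 degrees of freedom.
- τ = 0.2: noncentrality 0.8, significant in 11.6% of trials.
- τ = 0.3: noncentrality 1.2, 20.3%.
- τ = 0.5: noncentrality 2.0, 46.5%.

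**Simulation, 20,000 trials per setting.** The time-by-condition test is a repeated-measures F test on the change scores, with 2 and 30 degrees of freedom. Ranges run over the two correlations.

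| Common shift (SD) | One active condition significant | SRA or STEP significantly up, SOCIAL not | Time-by-condition significant |
|---|---|---|---|
| 0 | 5.1% | 4.0–4.8% | 5.1% |
| 0.2 | 11.6–12.3% | 13.5–19.4% | 4.9–5.1% |
| 0.3 | 20.1–20.5% | 19.5–29.3% | 5.0% |
| 0.5 | 46.3–47.0% | 26.3–37.7% | 4.8–4.9% |
| 0.7 | 74.3–74.5% | 18.7–23.8% | 4.9–5.1% |
| 0.9 | 92.0–92.3% | 7.0–8.1% | 4.8–5.0% |

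The third column is the pattern closest to the wording of the hypotheses. It falls again at large shifts, because SOCIAL then also becomes significant.

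**The case against.** The test that is wanted is already planned, for oxy-Hb and for the secondary outcomes. The primary question and hypothesis 2 both ask for a difference between conditions, and both hypotheses predict no gain after sitting, so a large common trend would contradict them. The question of how oxy-Hb changes over the session is a legitimate descriptive one. Ranking of tests is often left to an analysis plan that is not shown here. Practice before each testing leaves less room for learning between pre-test and post-test. The 1-back contrast protects oxy-Hb from any shift common to all loads. The Background links better performance with lower flow, so even the sign of a trend in oxy-Hb is uncertain.

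Most of this stands, and it limits the point. It does not remove it. The objection is to what is written: opening claims framed as uncontrolled change, and a primary-outcome hypothesis that names no test against SOCIAL. Practice runs reduce a trend but cannot be shown to abolish it.

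Three stronger readings are tempting and not supported:
- A reader might infer that the plan will treat a within-condition result as proof of a break effect. No sentence says so; it is a risk left open, not a decision rule.
- A reader might add cap repositioning to the causes. The Discussion says only "Repositioning of the cap during test days may also reduce accuracy in measurement from pre-test to post-test" and gives a forehead marker as mitigation. Random misplacement adds noise and does not by itself create a directional change.
- A reader might quote the chance that at least one active condition rises significantly, 64% to 71% at 0.5 SD. That ignores the hypotheses' prediction for sitting.

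**Conclusion.** The point holds as a matter of precedence. Controlled and uncontrolled tests stand side by side, and the opening claims of hypotheses 1 and 2 can be met by the uncontrolled one. Under common shifts of 0.2 to 0.5 SD, the false-positive rate is about 12% to 47% for one active condition and about 14% to 38% for the active-but-not-SOCIAL pattern, against about 5% for the time-by-condition test. These sizes rest on an assumed shift; that the time-by-condition test is immune to a shift common to all conditions does not. The exposure is most credible for n-back reaction time and accuracy, and applies to oxy-Hb only if the trend differs by load. It is worth correcting because the randomized control condition and the right test are already in place.

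**What to change.** In Statistical methods, state that effects of breaks on oxy-Hb and n-back performance are concluded only from the time-by-condition contrasts: SRA minus SOCIAL, STEP minus SOCIAL, and STEP minus SRA for intensity. Report within-condition changes as estimates with confidence intervals, labelled as change over the session. Say that the trigger for the correlation analysis refers to these contrasts.

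Recruitment finished in January 2021 and the hypotheses are published, so record this as a dated clarification of how hypotheses 1 and 2 will be judged and leave their text as it is.

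The models, data and sample are unchanged. With 16 participants a paired contrast has 80% power for an effect size of about 0.75, below the plan's smallest value of 0.9, provided that the plan's effect sizes apply to between-condition differences, which the article does not say. The cost is giving up stand-alone claims of improvement within a condition.

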Frequent, short physical activity breaks may be a more feasible alternative than a single bout, to counter the negative effects of prolonged sitting during a school day [25]. Studies have demonstrated positive effects of frequent, short physical activity breaks on peripheral vasculature in adults and older adults [26–30], but effects on cerebral vasculature remain elusive, especially in adolescents. In adults, studies performed using frequent, short physical activity breaks have been inconsistent, showing positive, negative, and no effects on cerebral blood flow [31–34] and on cognition [35–38]. Decreases in cerebral blood flow, with favorable effects on cognitive performance, have been seen in adult populations and suggest a potential neural efficiency adaptation [23, 24, 39, 40]. This suggests that after performing physical activity, efficiency in performing the cognitively demanding task increases so that less resources are required [39]. However, it remains unknown if a similar adaptation occurs in adolescents. Furthermore, studies that have measured cerebral blood flow have used indirect measurement modalities, such as transcranial Doppler ultrasound. One study using a more robust modality—functional near-infrared spectroscopy (fNIRS)—to study cerebral blood flow, found that male children with autism spectrum disorders had significant beneficial effects of a 20-min physical activity bout, compared to a sedentary counterpart, on prefrontal task-related cerebral blood flow [41]. Although performed in younger children (ages 8–10), another study found that after intermittent or continuous exercise, prefrontal-dependent cognitive performance improved compared to the baseline measure and this was significantly explained by alterations in cerebral blood flow assessed using fNIRS [42]. With fNIRS, it is possible to monitor cerebral blood flow by measuring changes in the attenuation of near-infrared light passing through the cortical tissue. Because fNIRS is non-invasive and does not require a certain posture or setting as in functional magnetic resonance imaging (fMRI), it is often used for brain imaging studies in infants and children [13]. It is considered a more feasible and robust option to measure cerebral blood flow changes, particularly when used in conjunction with short-separation channels, to eliminate the contaminating signal from blood flow in other tissues [43]. There are yet no studies investigating the effects of frequent, short physical activity breaks on hemodynamic changes using this technique in adolescents. We believe that the use of short-separation channels will produce partly different results.

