### Sample size

Studies with a similar design, and in children and youth are lacking. Thus, the sample size is based on studies of young and older adults. Using the data from these studies [18–20, 31, 77–79] software G*Power (Franz Faul, Universität Kiel, Germany, v 3.1.9.2) was used to calculate effect sizes. Effect sizes between 0.9 and 2.4 for the change in oxygenated hemoglobin were calculated, producing sample sizes between 6 and 13 participants (given an *α* = 0.05 and *β* = 0.8 assuming a two-tailed test). However, in order to have high enough variance within this age group, we will recruit 16 participants.

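### The correlation between changes in oxy-Hb and in cognition is stated as an unconditional question and hypothesis, but is analysed only if an undefined significance criterion is met

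*Protocol article*

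**What the plan says.** Three places in the protocol article bear on this.

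- Aims and research questions lists as a secondary question: "Are the changes in cognitive performance correlated with changes in oxy-Hb". No condition is attached.
- Hypotheses predicts it outright: "There will be a correlation between changes in oxy-Hb and cognitive performance". Again there is no condition.
- Statistical methods makes the analysis conditional: "Correlational analyses will be performed to investigate the association between changes in cognitive function and cerebral blood flow if significant changes are seen".

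The condition follows a description of mixed models for the secondary outcomes, "looking at both the within condition changes and the time-by-condition interaction effects". Both of these are effects on means. The text does not say whether oxy-Hb, cognition, either or both must change significantly, nor in which condition or n-back contrast. No unconditional analysis of this association appears elsewhere in the article. The sentence relating arterial stiffness and PWV to cerebral blood flow concerns a different relation.

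**The concern.** A correlation between individual changes measures how participants' changes move together around their averages. Adding a constant to every participant's change alters the mean but leaves the correlation as it was. A test of the mean is therefore the wrong criterion for deciding whether to look at the correlation.

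Two things are at stake. On a strict reading of the criterion, a hypothesis that the article commits to may never be tested, and readers would not learn whether the primary outcome is related to cognition. On a loose reading, the analysis goes ahead for whichever outcomes happen to reach significance, so the reported associations are a selected set. The article does not say which reading applies.

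**Working it through.** **Inputs from the protocol article.** Sample size: "we will recruit 16 participants". Alpha is 0.05, "assuming a two-tailed test". Planning effects: "Effect sizes between 0.9 and 2.4 for the change in oxygenated hemoglobin were calculated". There are two oxy-Hb variables (2-back against 1-back, 3-back against 1-back), six cognitive variables (reaction time and accuracy for each of three tests) and three conditions.

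**Assumptions.** The article gives no expected correlation and no expected cognitive effect. A correlation of 0.6 is assumed for the main illustration, with the same standardised mean change for both measures.

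**The plan's own figure.** For a paired t-test the noncentrality is d√n, with n − 1 degrees of freedom. At two-sided 0.05 and 80% power (the printed β = 0.8 is read as power), d = 0.9 needs n = 12 and d = 2.4 needs n = 4. The article states 13 and 6, so the figures are reproduced to within two participants. They do not size the correlation, for which no sample size or power is stated.

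**Power of one mean-change test at n = 16.** By the same formula it is 0.20 at d = 0.3, 0.46 at d = 0.5 and 0.92 at d = 0.9. At modest effects, a non-significant mean is a likely result.

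**Power of the correlation test at n = 16.** The statistic is t = r√(n − 2)/√(1 − r²), on 14 degrees of freedom. Because r is unchanged by a shift in either mean, its power does not depend on the mean changes. Simulated power is about 0.20, 0.53, 0.73 and 0.90 at true correlations of 0.3, 0.5, 0.6 and 0.7.

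**How often the gate opens.** The simulation used 20,000 trials of 16 bivariate-normal pairs of changes with correlation 0.6 and a one-sample t-test on each mean. The largest Monte Carlo standard error is √(0.25/20,000) = 0.0035, about 0.4 percentage points.

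| Mean change, both measures (SD) | Gate opens: both significant | Gate opens: either significant | Power of ungated correlation |
|---|---|---|---|
| 0 | 1% | 9% | 73% |
| 0.25 | 7% | 25% | 73% |
| 0.5 | 31% | 62% | 73% |
| 0.9 | 87% | 97% | 73% |

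The chance that the correlation is both run and significant is 0.5% (both) or 6% (either) at mean change 0, 21% or 44% at 0.5 SD, and 63% or 71% at 0.9 SD.

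**The loosest reading.** Suppose any significant within-condition change opens the gate. There are (2 + 6) × 3 = 24 such tests. With no true effect, and treating the tests as independent, the gate opens with probability 1 − 0.95^24 = 0.71. The tests are not in fact independent, so this figure is only indicative.

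**The case against.** The strongest reply is that the trial plans for large effects. If oxy-Hb changes by at least the lowest planning value, 0.9, and cognition changes as much, the gate opens in 87% or 97% of trials and little is lost. This stands, and it limits the size of the problem. It is not complete reassurance: the planning value is for oxy-Hb only, and Sample size acknowledges that comparable studies in children and youth are lacking and that adult data were used.

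A second reply is that an any-change reading would seldom block the analysis. That also stands, but it exchanges omission for data-driven selection.

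Three stronger readings are tempting, and the article does not support them.

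- A reader might infer that the Background itself foresees participants responding in opposite directions and cancelling in the mean. It does not. The neural-efficiency passage, "Decreases in cerebral blood flow, with favorable effects on cognitive performance, have been seen in adult populations", describes a shift in one direction, which would move the mean and tend to open the gate. The mixed increases, decreases and null results cited earlier in the Background are differences between studies. Cancellation is possible, but the article does not describe it.
- A reader might infer that three visits from 16 participants (3 × 16 = 48 pairs) will be pooled as independent. The article says only that correlational analyses will be done, and the method may properly be left to the analysis plan.
- A reader might say that the analysis is dropped exactly where it matters most. That is a judgement. What can be said is that it may be dropped when means do not change significantly, although an association may still be present and informative.

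**Conclusion.** The concern holds in a limited form. The article states a question and a hypothesis without condition, then makes their only analysis conditional on an undefined criterion that does not bear on them. A stated hypothesis can go untested, or the reported associations can be selected by significance.

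The size depends on the reading of the criterion and on the true effects. For one pair of measures the gate opens in as few as 1% of trials (no mean change, both required) and as many as 97% (0.9 SD, either sufficient). The harm is concentrated where effects fall short of those planned. These figures rest on the assumed correlation of 0.6, equal standardised mean changes in the two measures, and normally distributed changes. That the sections conflict, and that a correlation does not depend on the means, rests on none of these assumptions. Taking the criterion to mean significant mean changes is an inference, but it is the natural one from the tests described beside it.

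**What to change.** Delete the closing condition from the sentence on correlational analyses. Report the association between oxy-Hb change and cognitive change for each n-back load, with a 95% confidence interval, whether or not the mean changes are significant.

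Use a method that respects the repeated visits and keeps the between-participant association. One example is a mixed model of cognitive change in which oxy-Hb change is split into a participant mean and a within-participant deviation. A purely within-participant (repeated-measures) correlation is not enough, because it removes stable differences between participants. In simulation with an association only between participants (true correlation 0.9, between-participant variance share 0.5 or 0.7), it detected the association in 5% of trials, which is its false-positive rate. Correlating participant means detected it in 86% and 98%.

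If the authors prefer to keep a condition, Aims and Hypotheses should say that the question is conditional, and the criterion should name the outcomes, conditions and contrasts that count.

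The cost is one deleted clause and an analysis of data that the trial collects anyway. At n = 16 the intervals will be wide and should be presented as such.
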